#### 2.5.2. Experimental Group

Participants in the intervention group will be subjected to the following tests:-At the beginning of the intervention, a determination of glycosylated hemoglobin, blood pressure, lipid profile, weight, height, and TUG, 10MWT, and 5STS, which will be repeated after 12 weeks of intervention.-Before each training session, participants will undergo a basal blood glucose and blood pressure measurement, which will be repeated after the end of the session.-Each training session on the vibrating platform is composed of 6 exercises, with a duration of 60 s, with 60 s pauses between exercises and a warm-up exercise:

**Warm-up exercise: classic squat**

Prior to the training session, the subjects will place their feet on the floor at shoulder height, with their arms stretched forward to gain stability; the knee will be reflected at 100° and the back will be kept straight, returning to the starting position.

1.Alternating feet exercise.

With the back to the platform and the feet completely straight, the subjects will bend the knee while keeping the other leg straight. Then, they will alternate and do the same with the other leg for the duration of the exercise.

2.Up and down exercise.

Starting from the standing position on the platform, subjects will lower the right–left foot and then raise the right–left foot, repeating the exercise for 60 s.

3.Stride exercise

The subjects, starting from the initial standing position, will be separated at shoulder width and then place one foot on the platform, bending the knee at 90°, and the other on the floor. The exercise will be carried out with both legs alternately, holding the handlebars of the platform to maintain balance.

4.Heel Raise Exercise

The subjects, starting from the initial standing position, will be separated at shoulder width and raise their heels, keeping their knees slightly bent, their back straight, their eyes straight ahead, and holding the handlebars of the platform to maintain their balance.

5.Squat exercise

Starting from a standing position, shoulder-width apart, the subject will perform a 100° knee flexion, returning to the starting position.

6.Squat exercise with weight changes.

Starting from the squat position, the subject will perform a knee flexion–extension while shifting body weight in the mid-lateral axis (left–right) alternately.

### 2.6. Study Schedule

During the first week of February, detailed information on the procedure, informed consent, and the schedule of the study interventions will be provided. 

During the second week of February, preintervention measurements of HbA1c, lipid profile, blood pressure, height and weight, and TUG, 10MWT, and 5STS will be carried out so that they can be compared with the postintervention measurements.

During the following 12 weeks, the experimental group will carry out the intervention by means of the exercises in the WBV. These exercises will be performed three days a week, with a rest of at least 24 h between days of intervention.

In the third week of May, after the end of the intervention, the participants will again undergo HbA1c, lipid profile, weight, height, and TUG, 10MWT, and 5STS tests. The control group will also have their blood pressure measured (Figure 2).

### 2.7. Statistical Analysis

A descriptive analysis will be performed for the experimental and control groups. Similarity between groups will be calculated at baseline and differences between groups at 12 weeks will be examined. The variables HbA1c, lipid profile, weight, height, and blood pressure will be selected in bivariate analyses. Adjustment for confounding factors will be examined by linear regression. Questionnaire scores will be assessed and changes between baseline and 12 weeks between groups will be sought. Statistical analysis will be performed using IBM SPSS statistics version 28.0.

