## 2. Materials and Methods

The hypothesis of this study will be that the use of whole-body vibration has an effect on type 2 diabetes mellitus by decreasing the levels of glycosylated hemoglobin and blood glucose.

The objective of the study will be to analyze the decrease in glycosylated hemoglobin and blood glucose levels after the use of whole-body vibration platforms at baseline and at 12 weeks in people diagnosed with type 2 diabetes mellitus.

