### 2.2. Participants

The study will be carried out with diabetic patients from the Plasencia area. Participants who wish to participate in the present study must meet the following inclusion criteria: healthy type 2 diabetic patients between the ages of 50 and 60 years who are not taking medication for diabetes. Exclusion criteria will be established as having some underlying pathology (such as diabetic retinopathy or diabetic nephropathy), mobility disability and/or comorbidities incompatible with physical exercise and the use of vibration platforms, previous hip or knee surgeries, cognitive impairment, and neurological pathology.

Given the lack of studies that allow us to calculate the sample size for the sample to be representative, a pilot study will be carried out to obtain these data. A total of 40 subjects (20 men and 20 women) will be evaluated, divided into a control group (n = 20) and an experimental group (n = 20) (Figure 1).

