### 2.3. Variables

Anthropometric measurements such as weight, height, and waist–hip ratio will be taken. In addition, functional tests such as Time Up and Go (TUG), 10 Meters Walk Test (10MWT), and 5 Sit To Stand (STS) will be performed. Finally, capillary blood samples will be taken to measure HbA1c and plasma glucose and lipid profile. In addition, blood pressure, weight, and height values will be collectd.

HbA1c is a blood test to determine the average level of glucose or sugar in the blood during the last two or three months [11]. According to the ADA for the diagnosis of diabetes, HbA1c should be at values greater than or equal to 6.5% (≥48 mmol/mol); however, normal HbA1c values should be below 5.7%. The Affinity A1c Analycer^®^ (Debramedix Slne laboratory, Spain)will be used. The HbA1c analysis is a simple test, which consists of obtaining a few drops of capillary blood from a fingertip using a lancet and transferring them to the Affinity A1c Analycer^®^. HbA1c will be taken at baseline and at 12 weeks post procedure to identify variations after VBW.

Regarding capillary glucose, it is a capillary blood glucose measurement using a glucometer (FreeStyle InsuLinx glucometer^®^, Abbott laboratory, Spain) to determine glucose values and facilitate self-monitoring of DM. Obtaining a capillary blood glucose sample is necessary to verify that participants are in optimal conditions to perform the training session (blood glucose levels lower than 90 mg/dl or higher than 250 mg/dl prevent participants from performing the exercises) and also to verify the effect of whole-body vibration (WBV) on the behavior of blood glucose 48 h after the previous session [11].

The LUX^®^ meter (Debramedix Slne laboratory, Spain) will be used for the quantitative measurement of blood parameters such as total cholesterol, HDL cholesterol, and LDL cholesterol (calculated). As with the HbA1c, it is a simple test, which consists of obtaining a few drops of capillary blood from a finger of the hand using an auto-lancet Vitrex Sterilance (Debramedix Slne laboratory, Spain) and pouring them into the LUX^®^ meter. The lipid profile should be below 200 mg/dL for total cholesterol, 40 mg/dL or higher for HDL cholesterol, and less than 100 mg/dL for LDL cholesterol and should be taken at baseline and at 12 weeks after the start of the procedure to identify variations after VBW [13].

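### Section 2.7 leaves the comparison model open: the baseline value is never named as a covariate, and change from baseline is tied to questionnaires the trial does not list

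*Protocol article*

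**What the plan says.** Section 2.7 (Statistical Analysis) of the protocol article contains four relevant statements:

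- The group comparison: "Similarity between groups will be calculated at baseline and differences between groups at 12 weeks will be examined".
- A selection step: "The variables HbA1c, lipid profile, weight, height, and blood pressure will be selected in bivariate analyses". Its purpose is not given.
- Adjustment: "Adjustment for confounding factors will be examined by linear regression". No factor is named.
- Change from baseline: "Questionnaire scores will be assessed and changes between baseline and 12 weeks between groups will be sought".

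Elsewhere, section 2 gives the aim: "The objective of the study will be to analyze the decrease in glycosylated hemoglobin and blood glucose levels". Section 2.3 says "HbA1c will be taken at baseline and at 12 weeks post procedure to identify variations after VBW". Sections 2.5.1, 2.5.2 and 2.6 place TUG, 10MWT and 5STS before and after the 12 weeks in both groups. Section 2.2 fixes 20 participants per group without a calculation: "Given the lack of studies that allow us to calculate the sample size for the sample to be representative, a pilot study will be carried".

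**The concern.** Baseline HbA1c is measured in both groups, yet its only stated use in 2.7 is a check of similarity. In a randomised trial a baseline difference is a chance event, so such a check is a poor guide to whether or how to adjust. Meanwhile the covariates are open and the most useful one, the outcome's own baseline value, is not named.

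The one sentence that would serve the stated aim, a comparison of changes, has questionnaire scores as its subject. No questionnaire appears among the variables, the group procedures or the schedule. The three functional tests, which are measured at both times, have no analysis in 2.7. Glucose, which is part of the hypothesis, is not among the variables listed there either.

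Two things are at stake: precision in a trial of 40 people, and a reported effect that could differ according to which adjustment is finally chosen.

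**Working it through.** **No figure to reproduce.** The article gives no SD, effect size, significance level, power or correlation.

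**Inputs.** From the documents: n = 20 per arm (2.2), 1:1 allocation (2.1), outcome measured at baseline and 12 weeks (2.3, 2.6). Assumed: two-sided 5%, 80% power, equal SDs at both times, and r, the correlation between baseline and 12-week values, shown over a range.

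**Formulas.** Variance of the estimated group difference, relative to a raw 12-week comparison:

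- raw 12-week value: 1
- change score: 2(1 − r)
- baseline-adjusted regression (ANCOVA): 1 − r², times 1 + 1/(2n − 4) = 1 + 1/36 = 1.028 for estimating the slope at this size

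Detectable differences come from the noncentral t distribution (38 df for raw and change, 37 df for ANCOVA). The normal approximation for the raw case is (1.960 + 0.842) × √(2/20) = 0.886 SD; the t-based value is 0.909 SD.

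| r | Change variance | ANCOVA variance (large sample / n = 20) | Reduction against raw (n = 20) | Detectable: raw | Detectable: change | Detectable: ANCOVA |
|---|---|---|---|---|---|---|
| 0.3 | 1.40 | 0.91 / 0.94 | 6.5% | 0.91 | 1.08 | 0.88 |
| 0.5 | 1.00 | 0.75 / 0.77 | 23% | 0.91 | 0.91 | 0.80 |
| 0.7 | 0.60 | 0.51 / 0.52 | 48% | 0.91 | 0.70 | 0.66 |
| 0.8 | 0.40 | 0.36 / 0.37 | 63% | 0.91 | 0.58 | 0.55 |

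Detectable differences are in SD units.

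**Simulation check.** With 40,000 trials per value, the ANCOVA-to-raw variance ratio was 1.024 at r = 0, 0.769 at r = 0.5 and 0.529 at r = 0.7. The formula gives 1.028, 0.771 and 0.524.

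**Against a change score.** The large-sample ratio is (1 − r²) / [2(1 − r)] = (1 + r)/2, that is 0.75, 0.85 and 0.90 at r = 0.5, 0.7 and 0.8: a gain of 25%, 15% and 10%. With the factor 1.028 the ratios are 0.77, 0.87 and 0.925, so the gain at this size is slightly smaller, about 23%, 13% and 7.5%.

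**In terms of sample size.** At r = 0.7, 20/0.524 ≈ 38 per arm would be needed for a raw comparison to match the adjusted one.

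**Price.** One degree of freedom. If r were 0, variance would rise by about 3% and the detectable difference would move from 0.91 to 0.92 SD.

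**The case against.** The strongest reply is that the plan may already intend a change analysis. The aim is a decrease, HbA1c is taken twice to look for variation, and 2.6 says the first measurements are there to be compared with the later ones. The clause on changes in 2.7 may not be confined to questionnaires. This has force: if changes are what is meant, the relevant gain is the smaller one, about 25% to 10%. It does not settle the matter, because the text still attaches that sentence to an instrument the trial does not list, and ANCOVA has the smaller detectable difference at every r in the table.

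It can also be said that this is a 40-person pilot and that a separate analysis plan may name the model. Both lower the severity. The point therefore rests on what 2.7 states, not on detail it omits.

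A reader might infer more than the documents support:

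- *Adjustment would halve the variance.* That needs r of about 0.71, since 1 − 0.71² ≈ 0.50. No r is given.
- *Adjustment will be made only if baseline differs significantly.* The article states no such rule.
- *Covariates are chosen by bivariate screening, perhaps including 12-week weight or lipids.* The variables said to be selected are measured outcomes, and the purpose is unstated. The sentence may only mean that these variables enter the group comparisons.
- *Chance imbalance makes the raw comparison invalid.* Under randomisation it is unbiased, and its standard error already includes chance imbalance.

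**Conclusion.** The concern holds as one of precision and clarity, at moderate severity. Section 2.7 does not fix one model, does not name the baseline value, assigns the change comparison to an unlisted instrument and leaves out the functional tests.

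Relative to a raw 12-week comparison, adjustment for baseline would reduce variance by about 6% to 63% over r = 0.3 to 0.8. Both ends rest on an assumed r, equal SDs and the assumed error rates. Invalidity is not shown. What remains beyond precision is that open adjustment lets the reported effect depend on a choice made after the data are seen.

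**What to change.** Rewrite 2.7 along these lines:

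1. Main analysis: 12-week HbA1c regressed on group and baseline HbA1c, reporting the adjusted group difference with its 95% CI. The Discussion already says that the protocol focuses on HbA1c.
2. The same model, each outcome with its own baseline value, for lipids, blood pressure, weight, TUG, 10MWT and 5STS, using the February and May measurements in 2.6. Section 2.6 names blood pressure at the end only for the control group, whereas 2.5.2 repeats it in the experimental group; align the two.
3. State that neither baseline similarity nor bivariate results decide adjustment. Baseline values may still be described by group.
4. Replace the questionnaire scores with the functional tests.
5. Apply the model to glucose only after the sections are reconciled. Sections 2.3 and 2.5 mention plasma glucose, 2.5.2 ties glucose to training sessions, and 2.5.1 and 2.6 list no control-group measurement at baseline or 12 weeks.

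The cost is a few sentences. The regression is already foreseen and runs in the SPSS version named. No new measurements are needed for items 1 and 2, provided the blood pressure schedule is confirmed. Glucose may need one.

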### 2.8. Ethical Considerations

The study will be implemented in accordance with the Declaration of Helsinki and the ethical guidelines for medical research in humans. This study has been approved by the Bioethics and Biosafety Committee of the University of Extremadura (Registration No. 101//2023) and it has been registered at clinical.trial.org with the ID: (NCT 05968222). No patient identifiable information will be stored. Only the investigators will have access to the final data set of the study. It is considered that harm to the patient will be unusual because the tests performed will be those performed in the usual medical examination. However, participants will be free to leave the study if they wish to do so. Discontinuation of participation in the study may be made if the participant wishes to withdraw consent to participate, if the physician determines that continuation of the intervention is not indicated, or if the participant is unable to follow the study protocol. The likelihood of any health hazard during the procedure is minimal. If any serious adverse events occur, they will be reported according to the standard procedure for reporting serious adverse events in clinical research.

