#### 2.5.1. Control Group

Participants in the control group will undergo a determination of glycosylated hemoglobin, blood pressure, lipid profile, weight and height, as well as functional tests such as TUG, 10MWT, and 5STS. Subsequently, they will be encouraged to continue their normal life, insisting on the importance of glycemic controls before and after their daily physical exercise, in addition to continuing with the dietary measures recommended by their specialist. After 12 weeks, glycosylated hemoglobin, blood pressure, lipid profile, weight, height, and the TUG, 10MMT, and 5STS tests will be redetermined.

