## 3. Discussion

Aerobic physical exercise of moderate intensity is recognized as an effective nonpharmacological approach to reduce glycemia. The physiological modifications observed with WBV are analogous to those of any physical activity and, in addition to acute changes, chronic adaptations in the mechanical behavior of the muscles have been described. It is known that muscles react to vibration by contracting and stretching automatically. Vibration triggers a muscle contraction reflex, the TVR, which causes an increase in hormone secretion, among others [18]. That is why WBV could be a type of physical exercise to reduce glycemia and HbA1c, in addition to lipid profile, weight, height, functional balance, and neuropathic pain [12,19,20,21,22]. However, studies such as that of Behboudi et al. [23], after 12 weeks of whole-body vibration intervention, did not show a significant reduction in HbA1c. Another study by Liphardt et al. points in the same direction that bone quality in osteopenic postmenopausal women is not improved after 12 months of whole-body vibration training [24].

It is important to differentiate between vibratory devices that subject the body to vibration while the body is kept relaxed or resting on couches or beds (oscillatory-cyclic and oscillatory-cycloid vibration [3,12]) and WVB devices where the patient performs a voluntary exercise while adding the vibratory stimulus, affecting the whole body placed on top of a vibrating platform. It is a voluntary and conscious exercise to which the vibratory stimulus is added.

Since it is a physical exercise different from that practiced by the general population, it is new, and the sessions are of short duration, it could be estimated that the abandonment of the sample will only occur due to a very justified cause, which will reduce the negative results of the research.

HbA1C is one of the most determinant parameters in the diagnosis and long-term control of DM. According to the ADA [4], an HbA1c > 6.5% is considered a diagnostic criterion for DM, while values < 7.0% HbA1c determine good blood glucose control in the last four months.

This fact would behave as a protective factor in the development of certain cardiovascular diseases in people with DM 2, since it has been shown that the reduction in HbA1c in blood reduces the risk of developing heart disease by around 14% and, in addition, the risk of mortality [25,26].

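### The discontinuation rule can end study participation, not only the sessions, on grounds that apply almost only to the experimental arm, so 12-week outcomes may be lost selectively from that arm

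*Protocol article*

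**What the plan says.** Section 2.8 (Ethical Considerations) sets three grounds under one rule. The rule opens "Discontinuation of participation in the study may be made if the participant wishes to withdraw consent to participate" and continues "if the physician determines that continuation of the intervention is not indicated, or if the participant is unable to follow the study protocol". What may be discontinued is participation in the study. The article nowhere separates stopping the sessions from leaving the study.

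The two arms face very different demands:

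- **Experimental arm.** Section 2.6 schedules 12 weeks of training: "These exercises will be performed three days a week, with a rest of at least 24 h between days of intervention". Section 2.5.2 has glucose and blood pressure measured before every session. Section 2.3 uses both to judge fitness to train, and for glucose it gives limits: "blood glucose levels lower than 90 mg/dl or higher than 250 mg/dl prevent participants from performing the exercises".
- **Control arm.** Under section 2.5.1, "they will be encouraged to continue their normal life, insisting on the importance of glycemic controls before and after their daily physical exercise". Apart from dietary advice, nothing else is asked of controls until they are measured again after 12 weeks.

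Section 2.6 schedules the final measurements in the third week of May, and section 2.7 compares the groups at 12 weeks. On attrition, the Discussion says only that "it could be estimated that the abandonment of the sample will only occur due to a very justified cause".

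**The concern.** Withdrawal of consent has to end participation. The other two grounds are reasons to stop training; they give no reason to stop measuring HbA1c in May. Applied as written, the rule can turn a stopped intervention into a missing outcome.

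The loss would not be balanced. Controls have no intervention whose continuation could cease to be indicated. They could be unable to follow the protocol only by missing measurements or advice. It may also be related to the outcome, because the checks that decide whether a session goes ahead include glucose, which the objective names beside HbA1c. If the people removed from one arm differ in prognosis from those kept, the randomised comparison no longer compares like with like.

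The study is also the source for later planning: section 2.2 describes it as a pilot meant to supply the inputs of a sample-size calculation. A distorted difference or SD would carry over into that calculation.

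**Working it through.** **Is there a figure to reproduce?** No. The article gives no alpha, power, effect size, SD or dropout rate. The point rests on the text, and the arithmetic below only shows its possible size.

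**Which ground can apply to which arm**

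| Ground (section 2.8) | Experimental | Control |
|---|---|---|
| Withdrawal of consent | yes | yes |
| Intervention no longer indicated | yes | no intervention to stop |
| Unable to follow the protocol | 3 × 12 = 36 sessions to keep up | only missed measurements or advice |

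**Inputs.** From the article: 20 per arm (section 2.2). Assumed: k participants removed, from the experimental arm only; those removed would have ended m SD worse than those kept; no true effect; two-sided 0.05 normal test.

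**Bias.** The mean of all 20 equals the mean of those kept plus (k/20) × m. Dropping the k participants therefore shifts the arm mean by (k/20) × m SD.

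**False positives favouring vibration.** SE = √(1/20 + 1/(20 − k)), in SD units; rate = 1 − Φ(1.96 − bias/SE). The nominal rate is 2.5%.

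- k = 2: SE = √(0.0500 + 0.0556) = 0.325
- k = 4: SE = √(0.0500 + 0.0625) = 0.335

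| k removed | m (SD) | Bias (SD) | Rate favouring vibration |
|---|---|---|---|
| 2 (10%) | 0.5 | 0.1 × 0.5 = 0.05 | 3.55% |
| 2 (10%) | 1.0 | 0.1 × 1.0 = 0.10 | 4.92% |
| 4 (20%) | 0.5 | 0.2 × 0.5 = 0.10 | 4.83% |
| 4 (20%) | 1.0 | 0.2 × 1.0 = 0.20 | 8.63% |

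At m = 0 there is no bias, only lost precision. At negative m (those removed would have ended better) the sign reverses.

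**Upper bound.** Suppose exactly the highest 12-week values are lost. For a normal outcome, the mean after cutting off the top fraction p falls by φ(z)/(1 − p), where z is the (1 − p) quantile:

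- p = 0.10: 0.1755/0.90 = 0.195 SD, equivalent to m = 0.195/0.10 = 1.95
- p = 0.20: 0.2800/0.80 = 0.350 SD, equivalent to m = 0.350/0.20 = 1.75

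Simulation with 20 per arm (40,000 runs) gives slightly less, 0.182 and 0.331 SD. If removal instead follows a marker correlated 0.5 with final HbA1c, the simulated bias is 0.092 SD (k = 2) and 0.167 SD (k = 4), within the range in the table.

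**Scale.** With all 20 per arm, the SE of the difference is √(2/20) = 0.316 SD. The difference detectable with an assumed 80% power is (1.960 + 0.842) × 0.316 = 0.886 SD.

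**After the fix.** If everyone who stops is still measured, all 20 are compared with all 20, and this source of bias is zero.

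**The case against.** The strongest reply is that section 2.8 is a permissive ethics clause. It says participation may be ended, not that it must be, and it does not say that people who stop are left unmeasured. Section 2.6 has participants measured in May without exception, and a condensed article may leave post-discontinuation visits to the full protocol. This lowers the certainty but does not remove the point. The article states a rule here, and the rule ends participation; a reference to participants does not clearly cover someone whose participation has ended.

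Four stronger readings are tempting, and the documents do not support them.

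- **That barred sessions lead to withdrawal.** Section 2.3 bars a single session. Nothing sets a number of missed sessions or counts a barred one as failure to follow the protocol; a participant held back by the check is arguably following it. The link is possible, not stated.
- **That the rule necessarily favours vibration.** The session check has a lower limit of 90 mg/dl as well as an upper one of 250 mg/dl. Removals tied to the lower limit could act the other way. Participants are described as healthy and take no diabetes medication, and the article does not say which limit would be met more often.
- **That the upper bound is the likely size.** Removal would occur before the 12-week HbA1c exists, on session readings or clinical judgement, so it could not pick out exactly the highest final values.
- **That no analysis could help.** Baseline HbA1c and session glucose are recorded in the experimental arm, and methods using them could reduce the bias. Whether any is planned belongs to an analysis plan not at hand. Such methods rest on assumptions that a May measurement would make unnecessary.

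**Conclusion.** The concern holds as a defect of wording with a practical consequence. As written, section 2.8 permits outcomes to be lost almost only from the experimental arm, on grounds that may be related to glycaemic control. The between-group comparison could then be biased, in favour of vibration if those removed would have ended worse than those kept.

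Under the stated assumptions (2 to 4 of 20 removed, 0.5 to 1 SD worse) the bias is about 0.05 to 0.20 SD, with 0.195 SD (10% lost) and 0.35 SD (20% lost) as upper bounds. In the assumed range this is smaller than the sampling error of the comparison. It is systematic, however, and at the top of that range it raises the false-positive rate in favour of vibration from 2.5% to 8.63%. The removal rate, the gap in outcome and the direction are all unknown from the article, and if few are removed, as the Discussion expects of dropout, the effect is small. The change is worth making because it costs so little.

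**What to change.** Keep the clinical grounds for stopping sessions exactly as they are, and add two sentences to section 2.8:

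1. Stopping or missing sessions, for whatever reason, ends the intervention only and not participation in the study.
2. Everyone randomised is invited to the May measurements unless consent is withdrawn, and is compared in the group assigned.

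The May measurements are already in the schedule (section 2.6). The downside is at most a few additional measurements of people who stopped sessions.
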